### Outcomes

Prior to each study assessment, participants will be instructed to arrive in a fasting state and to abstain from caffeine, alcohol, nicotine and other stimulants for at least 12 hours before the visit. Whenever clinically safe and feasible, medications with known cardiovascular effects will be temporarily withheld prior to study assessments. For most POTS-related medications, a withholding period of at least 48 hours prior to testing will be applied. In participants receiving β-blocker therapy, particularly at higher doses, a gradual dose reduction over up to 72 hours prior to assessment is recommended, depending on the specific agent and dosage. All medication adjustments and temporary withholding procedures will be performed in consultation with the treating physician. Following completion of the respective study assessments, participants will resume their usual prescribed medication regimen unchanged for the remainder of the intervention period.

#### Procedure

On arrival at the study site, participants are welcomed, informed about the procedure and prepared for the examination.

Handgrip strength assessmentThe examination begins with a handgrip strength assessment performed in the seated position (see outcomes section for details). After completion of the handgrip test, participants rest briefly before further instrumentation.Simultaneous application of all monitoring devicesNext, all monitoring and measurement devices are applied simultaneously before the autonomic assessment begins. Continuous monitoring includes:

12-lead ECG for continuous HR and rhythm assessmentNon-invasive beat-to-beat BP monitoring using a finger-cuff systemSidestream capnography via nasal cannula for continuous end-tidal CO₂ (EtCO₂) measurementPulse oximetry attached to the left index finger for oxygen saturation

Supine phase—autonomic assessment (approximately 20 min total)The examination begins with a brief calibration phase of 2–3 min, during which all monitoring devices are calibrated and signals optimised, including finger-cuff BP system calibration.Once stable signals are confirmed, RSA is assessed using a standardised paced-breathing protocol. Participants are first familiarised with the breathing technique for 1 min using a visual pacer, then asked to maintain a breathing rate of 6 breaths per minute (0.1 Hz: 5 s inhalation, 5 s exhalation) for 2 min while ECG, beat-to-beat BP and EtCO₂ are recorded continuously. After completing the RSA assessment, participants return to spontaneous breathing and rest for 3–5 min to allow cardiovascular parameters to stabilise. Following this recovery period, a 10 min baseline recording is obtained while participants breathe spontaneously and remain still. This entire 10 min baseline phase is used for analysis to ensure optimal signal stability before proceeding to the tilt phase.Throughout the entire supine phase, HR (ECG), beat-to-beat BP and EtCO₂ are recorded continuously. Event markers are set to delineate the different assessment phases for subsequent analysis.Upright phase HUTT (15 min or until termination)Following the supine baseline, the tilt table is moved from horizontal to 70° within a few seconds and maintained in the upright position for 15 min or until intolerance occurs. Throughout the tilt phase, all haemodynamic parameters (ECG, beat-to-beat BP, EtCO₂, SpO₂) are recorded continuously. Symptoms will be documented using the Vanderbilt Orthostatic Symptom Score (VOSS),^28^ which evaluates nine orthostatic symptoms on a scale of 0–10.The VOSS is administered at the 10-minute mark or immediately on test termination. Additionally, the examiner continuously documents the type, onset time, and severity (0–10) of any newly occurring symptoms throughout the upright phase. The test is terminated early in case of syncope, presyncope, severe symptomatic hypotension, participant request or other medical concerns.

#### Primary endpoint

Our primary endpoint is the orthostatic HR change (ΔHR), derived from continuous 12-lead ECG (R-R intervals) throughout the protocol using the CNSystems Task Force Monitor (CNSystems Medizintechnik, Graz, Austria). ΔHR is defined as the mean HR during the 10-minute upright head-up tilt phase minus the mean HR during the 10-minute supine baseline period.

**ΔHR=mean HR during the 10-minute upright phase−mean HR during the 10-minute supine baseline**

#### Secondary outcomes

BP: Continuous beat-to-beat BP readings will be obtained using a non-invasive finger-cuff system and summarised into 1-minute averages. Additionally, brachial oscillometric BP measurements will be performed at baseline and every 3–5 min for calibration and verification. The outcomes include changes in ΔMAP, ΔSBP and ΔDBP, defined as the mean values during the 10-minute upright phase minus the mean values during the 10-minute supine baseline period. Additional outcomes include the presence of orthostatic hypotension according to predefined thresholds and initial orthostatic responses, such as the nadir SBP within the first 30 s after tilt-up and the time to recovery.

RSA: RSA is quantified as an index of cardiovagal parasympathetic function using the CNSystems Task Force Monitor (CNSystems Medizintechnik, Graz, Austria). RSA amplitude (ΔHR) is calculated using the peak-to-valley method, which determines the difference between maximum HR during inspiration and minimum HR during expiration for each breathing cycle, then averaged across all cycles during the 2-minute paced-breathing period, and expressed in beats per minute (bpm). Values are interpreted considering established age-related and sex-related variations in RSA.^29^

Breathing assessments: Symptoms of dysfunctional breathing will be assessed using the NQ, a validated 16-item self-report instrument. Items are rated on a 5-point Likert scale (0–4), yielding a total score of 0–64, with higher scores indicating greater symptom burden; scores ≥23 suggest clinically relevant hyperventilation syndrome. The NQ is widely used as a screening tool in clinical populations.^30^ In addition to self-report, breathing patterns will be assessed using the BPAT, a validated observational tool. A trained assessor will evaluate key features of dysfunctional breathing at rest, including thoracic versus abdominal movement, chest wall symmetry and use of accessory muscles. Items are scored based on severity and summed to provide an overall index of breathing pattern disturbance.

The BPAT has been shown to be a reliable clinical tool for identifying dysfunctional breathing patterns and is suitable for use in both research and clinical practice.^31^

Capnography: End-tidal carbon dioxide (EtCO₂) will be continuously monitored using a sidestream capnograph connected to a nasal cannula with an integrated sampling line. Measurements will be taken throughout the supine baseline period and during the upright tilt phase, with recordings synchronised with ECG and BP data. EtCO₂ values will be collected on a breath-by-breath basis and stored for offline analysis.^32^

Handgrip strength performance: Before and after the HUTT, participants will undergo a handgrip strength assessment using a CAMRY Digital Hand Dynamometer while seated. To evaluate muscle strength, fatigue and recovery capacity, a validated repetitive isometric handgrip strength protocol will be applied. Each participant will complete two rounds of a 10×3 s maximal isometric contraction test, separated by 1 hour. Within each round, participants will perform ten maximal contractions of 3 s each, with 5 s of rest between trials, paced by an interval timer. All measurements will be conducted in a seated position with the forearm supported and the hand in a neutral position.^33^

From this protocol, the following parameters will be calculated:

Maximum force (Fmax): The highest value of the 10 repetitions per round.Mean force (Fmean): Average of all 10 repetitions per round.Fatigue ratio: Fmax/Fmean of round 1. Higher values indicate greater force decline within a session (ie, higher fatigability).Recovery ratio: Fmean (round 2)/Fmean (round 1). Higher values reflect better recovery capacity between rounds.

This method allows for a more sensitive and objective evaluation of physical fatigue and recovery potential in older adults, beyond conventional HGS testing.

Activity and HR tracker: A wearable device (Fibion Flash) will monitor activity levels and HR for 3 days (2 nights) via ECG long-term adhesive electrodes at two points during the study: once in the first week and again after the 10th week of the intervention. This device provides a non-invasive, objective and real-time data collection method that tracks these metrics over an extended period. While the data are continuously collected and synced to a dedicated app or online portal, participants will not have access to real-time data such as HR, sleep, or activity levels to avoid influencing their behaviour. The collected data will be analysed by the research team.

Questionnaire management: Following the physiological measurements, participants complete the questionnaires either on-site (depending on the patient’s condition) or online at home.

MAPS: A German translation of the MAPS questionnaire, previously used in the study by Stick *et al*^34^ and used here with permission, will be employed in this trial. This questionnaire-based system helps individuals with POTS self-assess their symptom burden. It uses a visual analogue scale from 0 (no symptoms) to 10 (severe symptoms) to measure the severity of 12 common symptoms experienced over the past week. The total score can reach up to 120 points, providing a comprehensive assessment of symptom severity in POTS patients. Based on empirical data and clinical expertise, this scoring system allows for the systematic assessment and monitoring of the impact of POTS on patients’ daily lives by both patients and healthcare providers.^35^

SF-12: The validated German version of the SF-12 will be used. This 12-item patient-reported questionnaire assesses patient health across eight dimensions, including vitality, pain and general health perceptions. Each scale is converted to a 0–100 scale, with higher scores indicating better health and quality of life.^36^

HADS: The validated German version of the HADS (HADS-D) will be used. The HADS is a 14-item self-report questionnaire consisting of two 7-item subscales that evaluate anxiety and depression.^37^

Chalder Fatigue Questionnaire (CFQ): Fatigue severity will be assessed using the CFQ, a validated self-report questionnaire designed to measure physical and mental aspects of fatigue. The CFQ has demonstrated good reliability and validity in both clinical and community populations and will be used to quantify subjective fatigue severity at the time of assessment.

NQ: Symptoms of dysfunctional breathing will be assessed using the NQ, a validated 16-item self-report instrument. The questionnaire has demonstrated high sensitivity and specificity for distinguishing individuals with hyperventilation-related symptoms from healthy controls and is suitable as a screening tool in clinical and research settings.^38^

AEs: Participants will be encouraged to report any new or unusual symptoms to the study team promptly. This could be done via phone, email or during routine check-ins. These events, regardless of whether or not they are related to the study, will be recorded and monitored by the team. Discontinuation due to AEs: If a participant chooses to discontinue the intervention due to a perceived decline in health or adverse reactions, this will be documented and analysed. To ensure accurate and consistent data, participants might be asked to complete a simple AE questionnaire on a weekly basis. This could be administered as an online survey or over the phone, depending on the participant’s preference. If any severe or concerning symptoms arise, participants will be instructed to contact the study team immediately. All collected data will be systematically recorded and evaluated to monitor the safety of the intervention.

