### Statistical methods

Statistical analyses will be conducted using IBM SPSS Statistics version 28.0 for Windows (IBM). Continuous variables will be expressed as mean±SD deviation (SD), while categorical variables will be shown as frequencies and percentages with 95% CIs. The primary endpoint, HR change (ΔHR), defined as the difference between upright and supine HR, will be analysed using repeated-measures ANOVA with Bonferroni correction applied to account for multiple comparisons. The main comparison will focus on the change in ΔHR from baseline to week 12 across the four intervention groups. Exploratory secondary analyses will examine changes in BP, HRV, RSA, handgrip strength and patient-reported outcomes (MAPS, CFS, SF-12, HADS). For these outcomes, linear regression models incorporating baseline values, age, sex and medication as covariates will be employed. Interaction terms for time-by-group will be included to identify potential differences in trajectories over time. Assumptions of normality and homoscedasticity will be assessed with QQ-plots and residual plots. When appropriate, non-parametric methods will be used for sensitivity analyses. Analyses will follow the intention-to-treat principle, including all randomised participants according to their allocated intervention group, regardless of adherence or protocol deviations. An additional per-protocol analysis will be performed as a sensitivity check, limited to participants with ≥80% adherence to the intervention protocol. Missing data will be addressed through multiple imputation under the assumption of missing at random. Sensitivity analyses will also be conducted using last observation carried forward and complete-case analysis to evaluate robustness. Regarding the results, study nurses will systematically document reasons for missing data in the case report forms. All confirmatory tests for the primary outcome will be two-sided, with a significance level set at α=0.05, adjusted for multiple comparisons using Bonferroni correction. P values from secondary analyses will be considered exploratory and interpreted accordingly.

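### The handgrip fatigue ratio Fmax/Fmean ignores the order of the ten contractions, so it indicates force decline only if force peaks early and then falls; an order-based index should sit beside it

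*Protocol article*

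**What the plan says.** The Protocol article, Secondary outcomes, handgrip strength performance, sets out the test: "Each participant will complete two rounds of a 10×3 s maximal isometric contraction test", and within each round "participants will perform ten maximal contractions of 3 s each, with 5 s of rest between trials". The two building blocks are "Maximum force (Fmax): The highest value of the 10 repetitions per round" and "Mean force (Fmean): Average of all 10 repetitions per round". The fatigue index and its interpretation follow: "Fatigue ratio: Fmax/Fmean of round 1. Higher values indicate greater force decline within a session", which the text equates with higher fatigability.

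Nothing in the section requires the maximum to come from an early contraction. The other derived parameter, the recovery ratio, compares the means of the two rounds. None of the four listed parameters uses the order of contractions within a round.

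The section introduces the test with the words "a validated repetitive isometric handgrip strength protocol will be applied" and cites a source. Statistical methods gives the outcome its status: "Exploratory secondary analyses will examine changes in BP, HRV, RSA, handgrip strength and patient-reported outcomes".

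**The concern.** Decline within a session is a statement about sequence: later contractions are weaker than earlier ones. A ratio of the largest value to the average carries no information about sequence. It measures how far the peak stands above the mean. A participant who warms up or learns the task, one with a single unusually strong effort, and one who tires steadily can all obtain the same score.

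The maximum of ten unequal values also always exceeds their mean. Uneven effort alone therefore pushes the ratio above 1, and the more uneven the effort, the higher the score.

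At stake is how a change or difference in this parameter is worded. Steadier effort at the week-12 visit could be reported as reduced fatigability, and uneven effort as increased fatigability. No other listed handgrip parameter would show the error, because this is the only one aimed at fatigue within a round.

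**Working it through.** **Inputs.** From the article: ten contractions per round, Fmax as the largest of the ten, Fmean as their average, and the ratio taken from round 1. The article gives no handgrip data, so force values (30 to 21 kg), contraction-to-contraction CVs and sizes of decline are assumptions. It states no handgrip figure to reproduce.

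**Step 1: order (no assumption needed for the principle).** Fatigue ratio = max(x1…x10) / mean(x1…x10). Both terms are unchanged by reordering.

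| Record (kg) | Fmax/Fmean | Mean of first three / mean of last three |
|---|---|---|
| Falling 30, 29, …, 21 | 30/25.5 = 1.176 | 29/22 = 1.318 |
| Rising 21, 22, …, 30 | 30/25.5 = 1.176 | 22/29 = 0.759 |
| 30 first, then nine at 25 | 30/25.5 = 1.176 | 26.67/25 = 1.067 |
| Nine at 25, then 30 last | 30/25.5 = 1.176 | 25/26.67 = 0.938 |

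**Step 2: variability without decline.** I simulated 200,000 records of ten independent normal contractions with no trend. Mean Fmax/Fmean was 1.046, 1.077, 1.123 and 1.154 at CVs of 3%, 5%, 8% and 10%. Over the same range the first-three/last-three ratio averages 1.000 to 1.003.

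For scale, a noise-free linear decline by a fraction D from first to tenth contraction gives a ratio of 1/(1 − D/2): 1.053 for D = 10%, 1.081 for 15% and 1.176 for 30%. This sets noisy flat records against noise-free decliners, so it shows only that the ratio has a noise-dependent floor. It does not show how often people would be misranked.

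**Step 3: a like-for-like comparison.** Here decliners carry the same noise as flat performers. For the correlations, the true linear decline was drawn uniformly from 0% to 40%. For the pairs, one flat record was compared with one record declining by 15%.

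| Assumed CV | Correlation with true decline: Fmax/Fmean | Correlation: first three / last three | Flat outscores 15% decliner: Fmax/Fmean | Same: first three / last three |
|---|---|---|---|---|
| 3% | 0.93 | 0.97 | 3% | about 0% |
| 5% | 0.84 | 0.93 | 17% | 1% |
| 8% | 0.68 | 0.86 | 32% | 9% |

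At equal noise the mean ratio does rise with decline. At CV 5% it is 1.077 when flat, 1.116 with a 15% decline and 1.197 with a 30% decline.

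**The case against.** The strongest reply is that the reading fits the test. Ten maximal contractions with short rests are meant to make force fall, and where it falls the maximum comes early. With a simulated 20% linear decline, it lies in the first three contractions in about 98%, 90% and 79% of records at CVs of 3%, 5% and 8%. A steady rise across ten maximal efforts is a counterexample that nothing in the article predicts. The article also calls the test protocol validated and cites a source that is not available here, so replacing its index would cost comparability. All of this stands. It supports keeping the ratio, but it does not make the unconditional interpretive sentence correct.

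A reader might go further in three ways that the article does not support:

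- **That the ratio is uninformative and should be dropped or demoted.** The correlations show that it tracks decline, with more noise than an order-based index.
- **That misranking is the rule.** A flat performer with 8% CV does outscore a 15% decliner with 3% CV in 72% of simulated pairs, but that figure comes from giving the two participants unequal noise. At equal CV it is 3% to 32%, and against a 30% decliner it is about 0%, 0.4% and 7%.
- **That the comparison between arms is biased.** Practice and steadier effort at a second visit are common to randomised arms and largely cancel. A false arm effect would need an intervention that alters variability without altering fatigability. Participants know their breathing arm, and the Blinded parties section says that the nurse taking the physiological measurements is unblinded. A difference in effort between arms is therefore conceivable, but nothing in the article demonstrates one.

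It might also be said that the analysis plan can settle this. The point is not a missing detail, however: the formula and its interpretation are both printed, and they do not match.

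**Conclusion.** The point holds in limited form. That the ratio ignores order follows from the definitions alone, as does its tendency to exceed 1 without decline. The statement that higher values indicate greater force decline is therefore true only when force peaks early and then falls over the round.

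The practical loss is moderate and depends on the noise. Correlation with true decline is lower by 0.04, 0.09 and 0.18 than for the order-based index at CVs of 3%, 5% and 8%. These sizes rest on assumed CVs, linear declines and independent normal errors, because the article has no handgrip data.

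The outcome is one of four handgrip parameters in an exploratory analysis. The impact is minor, and the primary endpoint, alpha and sample size are untouched. The change is still worth making, because it is nearly free and prevents a change in consistency of effort from being reported as a change in fatigability.

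**What to change.** 1. Keep Fmax/Fmean as the ratio listed under the cited handgrip protocol.
2. Add one order-based index from the same ten round-1 values: the mean of the first three contractions divided by the mean of the last three, or the fitted slope over contractions 1 to 10 as a percentage of starting force. Choose one before outcome data are examined.
3. State that a difference in Fmax/Fmean will be interpreted as fatigability only if the order-based index agrees.
4. Reword the interpretation to say that the ratio measures peak relative to mean force, and reflects decline only when force falls over the round.

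The cost is one extra derived variable and one edited sentence. No new measurement or visit is needed, provided the ten individual values are stored in sequence; calculating Fmean already requires the values themselves. Comparability with other uses of Fmax/Fmean is preserved because the ratio stays.

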### Harms

Harms are defined as any AEs or side effects occurring during the trial, regardless of their causal link to the intervention. They will be assessed systematically through weekly AE questionnaires, supplemented by spontaneous reports from participants via phone, email or during visits. All events will be recorded in the case report form, including their severity, onset and duration. Discontinuation owing to AEs is permitted at any time, and reasons will be documented. Severe or concerning symptoms will prompt immediate contact with the study team. This structured monitoring ensures that both subjective complaints and objective safety concerns are consistently captured. The participant timeline and assessment schedule are detailed in figure 1.

**Figure 1 F1:**
[figure not shown]
Study design, assessment schedule, and intervention procedures.Participant timeline. ^a^List target time points and acceptable time windows in this row (eg, ±3 days). ^b^Active AVNT (Auricular Vagal Neuromodulation Therapy): 60 min daily using Nurosym device; SDB (slow deep breathing): 4 s inhalation, 6 s exhalation, 2–3 s pause; NB (normal breathing): spontaneous breathing pattern. ^c^Sham AVNT uses a sound-sham method with the same device placement but no electrical stimulation. Primary endpoint: orthostatic HR change (ΔHR−Delta HR)=mean HR during the 10-minute upright phase minus mean HR during the 10-minute supine baseline period. Medication washout: cardiovascular medications (beta-blockers, ivabradine, midodrine) discontinued 48 hours prior to physiological assessments. Study duration: 12 weeks total intervention period. Close-out visit=final endpoint measurements. BP, blood pressure; BPAT, Breathing Pattern Assessment Tool; HADS, Hospital Anxiety and Depression Scale; HR, heart rate; MAPS, Malmö POTS Symptom Score; POTS, Postural Orthostatic Tachycardia Syndrome; SF-12, Short Form Health Survey, PSQI, Pittsburgh Sleep Quality Index.

